### Exercise group protocol

The SRA will assess the baseline health and fitness of the participants of the Exercise Group using an exercise screening form that includes the revised Physical Activity Readiness Questionnaire (PAR-Q)[40], and other screening questions for exercise contraindications and precautions. If any exercise contraindications (e.g. shortness of breath, severe headache, sudden onset of numbness or weakness) is present, the participant will be excluded from the study and referred to their family physician for investigation. If any exercise precautions (e.g. fever, severe cachexia, extreme fatigue, sickness or bone pain) is present, high-intensity or high-impact exercise will be avoided initially. If severe nausea or painful calf is present, the participants will be advised to consult their family physician for further investigation and clearance prior to beginning the exercise program.

The SRA will provide each participant of the Exercise Group with a pedometer and a take-home package that contains pedometer and exercise instructions and precautions, daily logs, general exercise tips, stretching instructions and self-addressed envelopes. The pedometer instructions and daily log instructions are same as per Control Group protocol.

The Exercise Group will follow a walking exercise program that comprises a progressive structured exercise protocol and progressive target daily step counts regimen. The structured exercise protocol will initially begin with a 10-minute walking session, 3 sessions per week. The Exercise Group participants will be instructed to perform a 5-minute warm-up period by walking slowly, followed by a 10-minute walking workout period, and then a 5-minute cool-down period by walking slowly and a stretching routine that is in the Exercise Group taken-home package. The SRA will also demonstrate to the participants how the stretches are to be done.

Participants will use the Borg Scale of Ratings of Perceived Exertion (RPE) [41] to estimate their exercise intensity level during the workout and warm-up/cool-down periods. RPE is a reliable method in monitoring and regulating exercise intensity, with high correlation to oxygen uptake (r ≥ 0.83) [42] and high internal consistency at different levels of velocities and heart rates (α > 0.90) [43]. During the warm-up/cool-down periods, the participants will maintain an exertion level between 7.5 and 8 on (i.e. extremely light level of exertion). During the 10-minute walking workout session, the participants will gradually increase their walking speeds until they attain and maintain an RPE level between 9 and 13 (i.e. very light to light exertion) according to their baseline physical activity level (sedentary, moderately active, or active) as reported on their self-reported physical activity questionnaire. Sedentary individuals will start at RPE level of 9 (very light exertion), moderately active individuals will start at RPE level of 11 (light exertion), and active individuals will start at RPE level of 13 (somewhat hard exertion).

Each participant’s exercise level will be progressed every two week, first in frequency (1-day increment), then walking session (5-minute increment, and lastly RPE level. Based on the set progression protocol, the Exercise Group participants will be performing five walking exercise sessions per week, 30 minutes walking workout period per session, and will have attained RPE level of 15 (heavy exertion) by around 18 to 20 weeks. This level of exercise protocol will be maintained for the rest of the study period. The participants are instructed to record the date, start time, exercise duration and maximum RPE attained during each session in an exercise daily log.

The participants will also be encouraged to walk at their chosen pace at times outside their structured exercise protocol so as to achieve their assigned target daily step counts. The initial target will be set at 5000 steps for sedentary individuals, 6000 steps for moderately active individuals, and 7000 steps for active individuals. The target daily step counts will be progressed every two weeks (1000-steps increment) up to a maximum daily target of 10,000 steps. The participants will be counseled on the warning symptoms of impending cardiovascular events including chest pain or discomfort, shortness of breath, dizziness, severe headache, sudden onset of numbness or weakness, or painful calf suggestive of deep vein thrombosis. They will be strongly advised to discontinue the exercise program and report these symptoms to their attending physician and SRA immediately.

The SRA will call the Exercise Group participants every two weeks to monitor their safety, adherence, and progress using a short, structured phone survey. The results of the phone survey will be used to guide the adjustments/progression of the structured exercise and step counts protocols. In addition, the participants will return their pedometer and exercise daily logs every four weeks.

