**Methods:**

A 6-month prospective, single-blinded, randomized controlled trial will be conducted to compare the Exercise Group with the Control Group. Twenty men with prostate cancer starting ADT will be recruited and randomly assigned to one of the two groups: the Exercise Group will receive instructions in setting up an individualized 6-month home-based, walking exercise program, while the Control Group will receive standard medical advice from the attending physician. The primary outcomes will be psychosocial and cognitive functions. Cognitive functions including memory, attention, working memory, and executive function will be assessed using a battery of neurocognitive tests at baseline and 6 months. Psychosocial functions including depression, anxiety and self-esteem will be assessed at baseline, 3 and 6 months using the Center for Epidemiological Studies Depression Scale, Spielberger State-Trait Anxiety Inventory, and Rosenberg Self-Esteem Scale*.*

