#### Recruitment

A total of 20 patients will be recruited consecutively during office visits at the initial 3-month phase of the study at CancerCare Manitoba. The attending physician will screen the patients for inclusion criteria (men aged 50 or older, diagnosed with adenocarcinoma prostate cancer, will initiate and receive continuous ADT (LHRH or combination of LHRH and anti-androgen for at least 6 months). The physicians will be provided with an information sheet that provides brief information about study. If the patients meet the preliminary inclusion criteria, the physicians will provide a brief explanation about the study, and verbal consent to refer them to a clinical research nurse. The clinical research nurse will confirm that all inclusion and exclusion criteria are met, explain the study protocol, provide an information sheet for patients, and obtain written informed consent from the patients who would like to participate in the study. The clinical research nurse will provide the student research assistant (SRA) with the signed consent forms and contact information of the consented patients of the study.

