#### Baseline assessment session

The SRA, who is trained in health sciences field, will contact the participants to schedule a baseline assessment in coordination with a clinical psychology research assistant (CPRA), who is trained to administer neuropsychological tests.

The baseline assessment will be administered by the CPRA first, followed by the SRA. The CPRA will collect the sociodemographic characteristics, and administer the primary (cognitive-psychosocial functions) and secondary outcome measures (health related quality of life (HRQOL)). The SRA will collect data on the physical activity variables.

The CPRA will be blinded to the group assignments of the participants. After the baseline assessment, the SRA will assign the participant the first available number from a randomly generated list consisting of “1” and “2”, that are generated by mixed randomization, [38] using both simple randomization and permuted-block methods. Number “1” is designated as the Exercise Group that will receive instructions in setting up an individualized 6-month home-based walking exercise program in addition to their daily activities. Number “2” is designated as the Control Group that will be advised to perform daily activities as usual and follow the standard medical advice from their attending physician.

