### Control group protocol

The SRA will provide each participant of the Control Group with a pedometer to monitor his ambulatory activities. The participants will also be provided with a take-home package that includes written instructions, pedometer daily logs, and self-addressed envelopes. The participants will be instructed to wear the pedometer during waking hours, except while bathing, swimming or any procedures that do not allow metal parts to be close to targeted treatment area. The pedometer will be worn on a waistband, at or slightly anterior to the mid-axillary placement. A 50-step preferred-pace trial walk will be used to determine the side of pedometer placement. The side that yields the least percentage error in step counts will be the side for the individual’s daily application [39]. At the end of each day, participants will record the date, total daily time wearing the pedometer, and the number of daily steps taken, and then reset the pedometer to zero. Every two weeks, the SRA will call the participants to check for concerns and remind them to return their pedometer daily logs using the self-addressed envelopes.

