## Statistical analysis

### Primary outcome variables

A mixed between-within-subjects multivariate analysis of variance (MANOVA) (Group X Time) will be conducted to determine if there is a significant interaction between the between-subjects (Group) and within-subjects (Time) comparisons for:

cognitive function based on the neurocognitive tests at baseline and 6-month follow-up session;

psychosocial function at baseline, 3- and 6-month follow-up sessions;

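### The exercise contraindication screen comes after randomisation and in the Exercise Group only, and it excludes men from the study, so the comparison is open to selection bias

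*Protocol article*

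**What the plan says.** The order of events has to be pieced together from four sections of the protocol article.

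- **Recruitment.** Before consent, "The clinical research nurse will confirm that all inclusion and exclusion criteria are met". This applies to all men. The exercise screening form and the PAR-Q are not mentioned here.
- **Baseline assessment session.** "After the baseline assessment, the SRA will assign the participant the first available number from a randomly generated list". The student research assistant (SRA) therefore knows the allocation from that moment. In the part of the session before allocation, the SRA's stated task is to collect physical activity variables.
- **Exercise group protocol.** "The SRA will assess the baseline health and fitness of the participants of the Exercise Group using an exercise screening form". The form includes the revised PAR-Q and further questions, and the section sets three outcomes. A contraindication (the examples are shortness of breath, severe headache, and sudden numbness or weakness) means that "the participant will be excluded from the study and referred to their family physician for investigation". A precaution keeps the man in, with the exercise adapted at first. Severe nausea or a painful calf sends him for medical clearance before he starts.
- **Control group protocol.** "The SRA will provide each participant of the Control Group with a pedometer to monitor his ambulatory activities". Logs and fortnightly calls follow. No screening form and no exclusion step are described.

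For the primary outcomes, "A mixed between-within-subjects multivariate analysis of variance (MANOVA) (Group X Time) will be conducted".

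**The concern.** Randomisation makes the two groups comparable at the moment the number is drawn. Here a further selection step follows that moment and acts on one group only. A man who reports a contraindication leaves the study if he drew the Exercise Group and stays if he drew the Control Group. The groups that reach the 3- and 6-month assessments then differ by construction as well as by treatment.

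The person applying the step has just assigned the group and goes on to run the exercise programme. Blinding of the assessor who gives the cognitive and psychosocial tests offers no protection, because the selection happens before follow-up is measured. The loss is also hard to repair later: a man excluded from the study has no follow-up outcome for an analysis plan to restore.

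**Working it through.** The article states no power, effect size, dropout or contraindication rate, so there is no figure of the plan to reproduce. The check has two parts.

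**1. Does the text leave room for an innocent sequence?**

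- *The form might be completed before allocation.* It is described as a baseline assessment, but of Exercise Group participants, and that group exists only once the number has been drawn.
- *The nurse's check might already remove these men.* The symptoms given as contraindications do not appear in the Exclusion criteria section, so a man can pass eligibility and still be excluded by the form.
- *Exclusion might mean leaving the exercise programme only.* The article words the two differently. For warning symptoms during the programme, men are advised to discontinue the programme; for a contraindication on the form, exclusion is from the study.

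None of these readings fits the text.

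**2. How large could the bias be?**

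Inputs:

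- Total size: "A total of 20 patients will be recruited consecutively during office visits at the initial 3-month phase of the study", and they "will be recruited and randomly assigned to one of the two groups". The allocation ratio is not given; 10 per arm is assumed.
- q, the share of randomised men with a contraindication: not given; 5%, 10% and 20% are assumed.
- d, how much worse outcome change is in those men, in SD of change: not given; 0.5 and 1.0 are assumed.

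*Chance of at least one exclusion in the Exercise Group*, 1 - (1 - q)^10:

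- q = 5%: 1 - 0.95^10 = 0.40
- q = 10%: 1 - 0.90^10 = 0.65
- q = 20%: 1 - 0.80^10 = 0.89

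*Bias with no true treatment effect.* Let the mean change in men without a contraindication be m. The Exercise Group keeps only these men, so its expected mean is m. The Control Group keeps everyone, so its expected mean is (1 - q)m + q(m - d) = m - qd. The difference is q x d:

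| q | d = 0.5 | d = 1.0 |
|---|---|---|
| 5% | 0.025 | 0.05 |
| 10% | 0.05 | 0.10 |
| 20% | 0.10 | 0.20 |

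The range is thus about 0.03 to 0.20 SD. If d = 0 the bias is zero, and if d is negative it runs against exercise.

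A simulation with 10 men per arm, no treatment effect and 40,000 replicates per setting gave 0.050 and 0.097 SD at q = 10%, and 0.100 and 0.199 SD at q = 20%, for d = 0.5 and 1.0. This agrees with the formula; q = 5% was not simulated. When both arms were screened, or every randomised man was kept, the mean difference was within 0.003 SD of zero.

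**The case against.** **The excluded group is narrower than it may look.** A reader might infer that any positive PAR-Q answer removes a man, or that unfit men in general are removed. The text does not support this. Only contraindications exclude, and men with precautions such as extreme fatigue or severe cachexia stay in the Exercise Group. This stands and limits how large q can be.

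**Direction is not established.** A reader might conclude that the comparison is biased in favour of exercise, since the Background links cardiovascular fitness to cognition. But the named contraindications are symptoms, not measures of fitness, so that link does not carry over directly. Bias towards exercise is plausible if symptomatic men do worse over time, but the article does not show that they do. This also stands.

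**Level is not change.** The primary test is the Group x Time interaction, and baseline is measured before allocation. A stable difference in level between the arms cancels in that contrast; only a link between contraindications and change matters. This stands, and it is why d is defined on change.

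**The rate may be low.** The general exclusion criteria already remove many cardiac, vascular and neuromusculoskeletal causes of the named symptoms. That is a fair reason to include q = 5%.

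**Noise dominates.** With 10 per arm, the standard error of a difference in mean change is sqrt(2/10) = 0.45 SD, so 0.025 to 0.20 SD is 0.06 to 0.45 standard errors. The bias is small beside sampling error. But sampling error is what the test allows for; a selection effect is not, and it does not average out.

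**The article condenses a fuller protocol.** The Control Group section could be silent for brevity. That does not rescue the point, because the article positively states who is screened and what follows. If the full protocol screens every man before allocation, the article's wording is wrong and needs correcting.

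**Conclusion.** The defect is fixed by the text: a one-sided exclusion from the study after randomisation, applied by someone who knows the allocation. It leaves the randomised comparison open to selection bias. Whether the comparison will in fact be biased, and in which direction, cannot be read from the article, and no stronger claim is made here.

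The size rests on three assumptions that the article does not supply: about 10 men per arm, 5-20% with a contraindication, and outcome change 0.5-1.0 SD worse in those men. Under them, at least one exclusion is likely at the middle and upper rates and the bias is modest. The case for acting rests less on that size than on the fact that exclusions already made may not be repairable in the analysis, while preventing them costs almost nothing.

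**What to change.** Two changes of wording.

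1. In the Baseline assessment session, have the existing exercise screening form completed for every consented man before the random number is drawn, with its contraindication rule unchanged. Any exclusion then falls before allocation and equally on both arms. Remove the exclusion step from the Exercise group protocol.
2. State that nobody is excluded from follow-up or analysis after randomisation. Every randomised man keeps his 3- and 6-month assessments and is analysed in his assigned group, whether or not he exercises.

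Which symptoms bar or stop exercise is a clinical matter, and neither change touches it. Men with precautions, and men sent for clearance, remain in the trial as the article now provides.

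The cost is protocol wording and about 10 more short forms, for the men who would go to the Control Group, at a visit already scheduled. If 20 is meant as the number randomised, rather than the number recruited, then 20/(1 - q) men must be screened: 21 at q = 5% and 25 at q = 20%.

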#### Exclusion criteria

Patients will be excluded from the study if they have severe cardiac disease (New York Heart Association class III or greater), angina, pre-existing osteoporosis with T-score at or below −2.5, stable bone lesion, uncontrolled hypertension (blood pressure > 160/95 mm Hg), moderate to severe aortic stenosis, acute illness or fever, uncontrolled atrial or ventricular dysrhythmias, uncontrolled sinus tachycardia (> 120 beats per minute), third-degree atrio-ventricular heart block, active pericarditis or myocarditis, recent pulmonary embolism, deep vein thrombosis, uncontrolled diabetes, uncontrolled pain, cognitive impairment, history of falls due to balance impairment or lost of consciousness, or severe neuromusculoskeletal conditions that limit their ability to perform walking exercise (including ataxia, peripheral or sensory neuropathy, unstable bone lesion, severe arthritis, pathological lower limb fractures within 6 months, lower limb amputation).

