#### Follow-up sessions

The CPRA will schedule follow-up sessions for all participants at 3 and 6 months after ADT initiation. At 3 months, primary outcome (psychosocial functions) and secondary outcome variables (HRQOL) will be re-assessed. At 6 months, all primary (cognitive and psychosocial functions) and secondary (HRQOL) outcome measures will be re-assessed.

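### By protocol rule, the exercise screening form is applied after allocation to Exercise Group men only, and a contraindication removes the man from the study; the Control Group has no matching rule

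*Protocol article*

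**What the plan says.** Four sections of the protocol article fix the order of events.

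- **Recruitment and Exclusion criteria.** The clinical research nurse checks every man against the full eligibility list before taking written consent. The list covers many cardiac, vascular, neurological and musculoskeletal conditions. It does not mention the exercise screening form.
- **Baseline assessment session.** "After the baseline assessment, the SRA will assign the participant the first available number" from the random list. The SRA is the student research assistant. The form is not among the baseline tasks described there.
- **Exercise group protocol.** "The SRA will assess the baseline health and fitness of the participants of the Exercise Group using an exercise screening form". The form combines the revised PAR-Q with further questions on contraindications and precautions. The example contraindications are breathlessness, bad headache, and numbness or weakness of abrupt onset. If any is present, "the participant will be excluded from the study and referred to their family physician for investigation".
- **Control group protocol.** "The SRA will provide each participant of the Control Group with a pedometer to monitor his ambulatory activities". The section goes on to the take-home package, the daily logs and two-weekly calls. It contains no screening form and no exclusion rule.

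Under Follow-up sessions, "The CPRA will schedule follow-up sessions for all participants at 3 and 6 months after ADT initiation". Under Statistical analysis, the primary MANOVA tests for a "significant interaction between the between-subjects (Group) and within-subjects (Time) comparisons".

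**The concern.** Randomisation makes the two arms comparable at the moment the number is drawn. A rule that then removes men from one arm according to their health means that the groups compared at 3 and 6 months need not be the groups that were randomised. A Control man with the same symptoms on the same day is not asked about them on this form; he stays in and is assessed.

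The rule ends participation in the study, not just in the walking programme. On its ordinary reading, the removed man's later outcomes are not collected. An analysis plan that defined its population as all randomised men would then have no 3- or 6-month data for him. The article does not describe data collection after exclusion, so this is a reading of the exclusion rule and not a separate statement in the text.

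**Working it through.** The article states no contraindication rate, dropout rate, effect size or power, so there is no figure of the plan's own to reproduce. The check has two parts: the order of procedures, and a sense of scale under stated assumptions.

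**1. Order of procedures**

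| Step | Exercise Group | Control Group |
|---|---|---|
| Nurse's eligibility check before consent | yes | yes |
| Baseline assessment | yes | yes |
| Allocation number drawn | yes | yes |
| Exercise screening form | yes | no |
| Exclusion from the study on a contraindication | yes | no |

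The form is used on members of the Exercise Group, a group that exists only once the number is drawn. The example contraindications are not named in the Exclusion criteria, so the earlier check does not make the later one redundant.

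**2. Share of the arm removed**

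Inputs: 20 men in total and two groups (article). Arm sizes are not stated; 10 per arm is assumed, with 8 to 12 as a range.

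- One removal: 1/10 = 10% (1/8 = 12.5%; 1/12 = 8.3%).
- Two removals: 2/10 = 20% (2/8 = 25%; 2/12 = 16.7%).
- Control under this rule: 0%.

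**3. Chance that the rule is triggered**

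For 10 Exercise men and an assumed contraindication rate p, P(at least one) = 1 − (1 − p)^10, and P(at least two) = 1 − (1 − p)^10 − 10p(1 − p)^9.

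| Assumed p | Expected removals (10p) | At least one | At least two |
|---|---|---|---|
| 5% | 0.5 | 40% | 9% |
| 10% | 1 | 65% | 26% |
| 20% | 2 | 89% | 62% |

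**4. Effect on the Group by Time comparison**

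Let k of n Exercise men be removed, and let d be the mean change of the retained men minus the mean change that the removed men would have had. The mean change of the whole arm is [(n − k) × retained + k × removed]/n. The retained mean therefore differs from it by (k/n) × d.

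- Level difference only: a man who is lower by L at both visits has change (b − L + c) − (b − L) = c. L cancels, so d = 0 and the shift is 0.
- Change difference: with n = 10, the shift is 0.1 × d for one removal and 0.2 × d for two. If d were ±0.5 to ±1 SD of change (an assumption), the shift would be ±0.05 to ±0.10 SD for one removal and ±0.10 to ±0.20 SD for two. The article supplies neither the sign nor the size of d.

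**5. Precision**

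The standard error of a two-arm difference is proportional to √(1/n₁ + 1/n₂).

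- 10 v 10: √0.2000 = 0.447 (18 df).
- 10 v 9: √(1/10 + 1/9) = 0.459, up 2.7% (17 df).
- 10 v 8: √(1/10 + 1/8) = 0.474, up 6.1% (16 df).

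The loss of precision is small. The issue is comparability.

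**The case against.** The best defence is that little may come of the rule. The nurse has already screened all men, and the exclusion list removes severe cardiac disease, angina, uncontrolled hypertension and rhythm disorders, recent pulmonary embolism, deep vein thrombosis and neuropathy. Many serious causes of the listed symptoms are therefore gone from both arms before allocation. At an assumed rate of 5%, the chance that no Exercise man is removed is 0.95^10, about 60%. This stands as a limit on frequency. It does not make the rule symmetric.

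It could also be said that assessing baseline health implies a step before allocation. The same sentence restricts the form to the Exercise Group, so that reading does not hold. Even if it did, only one arm would be screened.

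A reader might infer more than the text supports in four ways.

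- **That only the Exercise Group can lose men through ill health.** Control men can also drop out through illness. The asymmetry lies in the protocol's rule, not in all attrition.
- **That the protocol itself shows exclusion to be unnecessary for safety.** For the same kinds of symptom arising later, it says of the men: "They will be strongly advised to discontinue the exercise program and report these symptoms to their attending physician and SRA immediately". That passage is silent on their study status, and a symptom present before exercise starts is a different clinical situation from one that emerges during it. Nothing follows from the silence.
- **That the decision is open to manipulation because the SRA knows the arm.** The rule as written is automatic and describes no discretion. The problem is the one-sided use of the form.
- **That the bias favours exercise.** This would need the removed men to be known to have the worse trajectory. The document does not say so, and a constant level difference cancels.

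**Conclusion.** The point holds as a defect in a stated rule. The form follows allocation, applies to one arm and leads to exclusion from the study, and nothing elsewhere in the article corrects this. Bias in the Group by Time comparison is possible but not shown. It arises only if removed and retained men would have changed differently, and its size and direction cannot be derived from the document. The scale figures rest on an assumed 10 men per arm and on assumed contraindication rates of 5% to 20%. Confidence is high on the order of procedures; no claim is made that the bias is material. No figure stated in the article changes. The change should be made because it is cheap and because outcomes not collected cannot be restored at analysis.

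**What to change.** Complete the exercise screening form on all men as the last step of the baseline assessment, and record the result before the allocation number is drawn. Exclude and refer men with contraindications at that point. For any contraindication found after allocation, state that it may only delay, modify or stop the exercise, and that every allocated man is followed at 3 and 6 months and analysed in the group he was allocated to. Exclusions after randomisation under this rule then become zero in both arms by design.

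The cost is protocol wording, a slightly longer baseline visit for men who go on to Control, and a few men lost before allocation, which may slow recruitment of the 20.

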#### Exercise group

*Exercise adherence* of the Exercise Group participants will be monitored using the exercise daily logs returned every four weeks, and phone surveys conducted by SRA every two weeks. The phone surveys will also be used to monitor *exercise safety and progress*.

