### Secondary outcome variables

Pearson product–moment correlation will be conducted to determine the association between HRQOL and primary outcome variables (cognitive and psychosocial functions).

For The Exercise Group, Spearman-Rank Or Pearson Product–Moment Correlations Will Be Performed To Determine If Baseline Sociodemographic, Clinical, Psychosocial, And Physical Activity Factors Are Significantly Associated With Exercise Adherence (Average Percentage Of Adherence To The Target Exercise Frequency, Duration And Intensity Based On The Exercise And Pedometer Daily Logs).

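### The exercise log records only each session's peak RPE, so intensity adherence based on it cannot show that the prescribed level was held

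*Protocol article*

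**What the plan says.** All references are to the protocol article.

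- **Prescription (Exercise group protocol).** During the workout, men are to "gradually increase their walking speeds until they attain and maintain an RPE level between 9 and 13", with the starting level set by baseline activity. They "will have attained RPE level of 15 (heavy exertion) by around 18 to 20 weeks", and then "This level of exercise protocol will be maintained for the rest of the study period".
- **Log (same section).** Men are told to "record the date, start time, exercise duration and maximum RPE attained during each session in an exercise daily log". Maximum RPE is the only intensity entry listed.
- **Adherence variable (Secondary outcome variables).** Adherence is defined as "Average Percentage Of Adherence To The Target Exercise Frequency, Duration And Intensity Based On The Exercise And Pedometer Daily Logs". It is correlated with baseline factors in the Exercise Group.
- **Pedometer log (Control group protocol; the Exercise Group follows the same instructions).** It holds the date, wear time and step count. None of these measures exertion.
- **Phone contact (Exercise group, under Data collection).** Adherence "will be monitored using the exercise daily logs returned every four weeks, and phone surveys conducted by SRA every two weeks". The survey has an operational use: "The results of the phone survey will be used to guide the adjustments/progression of the structured exercise and step counts protocols". Its intensity content is not described, and it is not named as a source for the adherence variable.

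**The concern.** The target is a level to be held through the workout, but the recorded value is the highest level touched. A man who reaches the target briefly and a man who holds it throughout write the same number. No scoring rule set later, in an analysis plan or elsewhere, can recover the held level from the peak. The problem therefore lies in data capture and is not a detail that a condensed article has left to another document.

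At stake is whether the intensity part of the adherence percentage measures what was prescribed. This matters most late in the programme. Progression runs every two weeks, first in frequency, then in duration, then in RPE. Read in sequence, 3 to 5 sessions takes 2 steps and 10 to 30 minutes in 5-minute increments takes 4 steps, so 6 × 2 = 12 weeks. After that, RPE is the only part of the structured exercise still being raised, and it is the part whose maintenance the log cannot show.

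**Working it through.** The document gives no adherence figure and no rule for turning log entries into a percentage, so there is no stated figure to reproduce. The check has a logical part, which needs no assumption, and an illustration, which does.

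**1. Logic.** For any session, maximum RPE ≥ RPE held for most of the workout. Equality holds if the man climbs to a level and stays there. As an example of the information lost, take a target of 15 with 28 minutes at RPE 11 and 2 minutes at RPE 15. The log shows 15, although the target was held for 2/30 = 7% of the workout.

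**2. Illustration.** These assumptions are not in the document: minute-by-minute RPE is normal around the sustained level and rounded to an integer; minutes are independent; the target is 13; the sustained level is 0, 1 or 2 points below target; the minute-to-minute SD is 0.5 or 1.0. Workouts last 10 or 30 minutes (the document's first and final durations), with 20,000 simulated sessions per setting.

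The peak pass rate can be checked by hand. If p is the chance that one minute rounds to at least 13, the chance that the peak of T minutes does so is 1 − (1 − p)^T. One point below target with SD 0.5, p = 0.16, so T = 10 gives 1 − 0.84^10 ≈ 0.82.

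| Sustained level | Workout (min), SD | Peak at or above target | At least half the minutes at target | Peak exactly at target |
|---|---|---|---|---|
| At target | 10, 0.5 | 100% | 100% | 18% |
| At target | 10, 1.0 | 100% | 94% | 3% |
| At target | 30, 0.5 | 100% | 100% | 1% |
| At target | 30, 1.0 | 100% | 99% | 0% |
| 1 below | 10, 0.5 | 82% | 1% | 81% |
| 1 below | 10, 1.0 | 97% | 16% | 48% |
| 1 below | 30, 0.5 | 99% | 0% | 95% |
| 1 below | 30, 1.0 | 100% | 2% | 13% |
| 2 below | 10, 0.5 | 1% | 0% | 1% |
| 2 below | 10, 1.0 | 50% | 0% | 44% |
| 2 below | 30, 0.5 | 4% | 0% | 4% |
| 2 below | 30, 1.0 | 87% | 0% | 70% |

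**3. Reading by scoring rule.**

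- *Peak at or above target.* For a man holding the target, the excess over the half-the-minutes criterion is 0 to 6 percentage points (100 − 94 = 6 at most). One point below, it is 81 (82 − 1, and 97 − 16) to 99 (99 − 0).
- *Peak divided by target, capped at 100%.* One point below, the peak ratio is 0.99 to 1.00 against a mean ratio of 12/13 = 0.92, an excess of 7 to 8 points. The size depends heavily on the rule.
- *Peak exactly equal to target.* Men holding the target score only 0% to 18%, so the error runs downward.

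**4. Effect on the correlations.** Under the at-or-above rule, the contrast between a man at target and a man one point below is 0 to 18 points on the peak (100 − 100 to 100 − 82). On the half-the-minutes criterion it is 78 to 100 (94 − 16 to 100 − 0). Between one and two points below, the peak gives 13 to 95 points (100 − 87 to 99 − 4), against 0 to 16 on the other criterion. The peak reorders and rescales differences between men, and no single direction follows for the correlations.

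**The case against.** The best case against is that the article gives no scoring rule and does not show the log form, which sits in the take-home package. A man who follows the instruction climbs to his level and stays there, so his peak is close to the level he held. The later target is itself worded as a level attained. Step logs and two-weekly phone surveys also show whether walking was done. The proposed held RPE is self-reported too, and nothing shows that it is recalled more accurately.

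Much of this stands, and it limits the size of the point. It does not remove the mismatch: the article lists the log entries, the only intensity entry is a peak, and the workout instruction is to hold a level. Neither steps nor the surveys as described supply a held RPE to the adherence variable.

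Stronger readings are tempting but not supported:

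- *Adherence is systematically overstated, with errors only upward.* This needs an at-or-above (or similar) rule and men who peak without holding. Under an exact-match rule the error reverses.
- *Duration adherence is inflated because warm-up and cool-down are logged.* The routine is a "5-minute warm-up period by walking slowly, followed by a 10-minute walking workout period, and then a 5-minute cool-down period", and the log has one duration entry. But the article mostly uses the word session for the workout itself, and nothing says that the slow-walking periods are entered. This would be an assumption about an unseen form.
- *The dose delivered is overstated, so a null result could not be interpreted.* No dose variable is defined, and the step logs and phone surveys also bear on whether the walking was done.

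**Conclusion.** The point holds in a limited form. As described, the log cannot verify that the prescribed intensity was maintained, and intensity adherence is liable to overstatement if a session counts once its peak reaches target. For men who hold the level as told, the bias is slight. For men just short of it, the bias may be anything from a few points to nearly all sessions, depending on a rule the article does not state and on variability that had to be assumed. Independent minutes also push the simulated peaks up; if exertion drifts slowly, the peak lies closer to the sustained level.

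The consequence is small. Intensity is one of three adherence components. Adherence enters only the Exercise Group correlations, in about 10 of the 20 men if allocation is equal (an assumption). The primary Group by Time MANOVA is untouched. The point is worth acting on because the remedy is cheap and an unrecorded level cannot be reconstructed afterwards. It falls away if the actual log form already records the level held.

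**What to change.** Add one entry to the exercise daily log: the RPE held for most of the workout period. Keep maximum RPE as an extra item. In the Secondary outcome variables section, say that intensity adherence is scored from the held RPE against that fortnight's target.

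The cost is a revised log form, a line of instruction when the take-home package is handed over, and one more self-reported entry per session. The adherence figure may also come out less favourable. The prescribed intensity and its progression stay as they are.
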